### Trial status

At the date of manuscript submission participant recruitment has been completed, and data collection has commenced but has not been completed.

### Sit-stand multi-component intervention

#### Theoretical basis and intervention development

The intervention to be delivered to the SS-MC arm aligns with the World Health Authority’s promotion of a healthy workplace model [31]. This theoretical framework emphasises that best-practice workplace health interventions should involve an integrated approach involving organisation and individual level approaches to behaviour change [32]. This is based on an ecological definition of health and approach to behaviour change, which recognises that many factors influence health behaviour and that psychosocial influences on physical activity and sedentary behaviour vary in different contexts [25,33]. The content of the intervention will be based on previous interventions in a similar context e.g. [26,34,35] and will incorporate behaviour change techniques, including motivational interviewing [36,37]. The multi-component intervention will be refined to reflect the specific context (based on discussion with the respective organisation) and employee’s needs (following the ‘personalised inception conversation’, see below) [38]. The intervention will take effect for the first six-months following the installation of sit-stand workstations.

#### Multi-component intervention procedures

The multi-component intervention comprises organisational, environmental, and individual level elements, in accordance with the healthy workplace model [31]. For an overview of the intervention procedures within the overall context of the study please see Figure 1*.*

##### Organisational level procedures

These procedures aim to enhance the participants’ perceived level of organisational support for the sit-stand workstation intervention*.* It will consist of four emails to participants in the SS-MC arm from organisational managers who are responsible for workplace wellbeing. These emails will be sent one week before the installation of the workstation, and at weeks 6, 14 and 24 following the installation of the workstations. Emails will provide information on (a) explicit organisational support for using sit-stand workstations (motivational information) (b) the negative health impacts of sitting at work, and (c) strategies to reduce sitting and increase standing in the workplace.

##### Environmental level procedures

The environmental element will involve changes to the physical environment that are expected to facilitate reduced sitting and increased physical activity. A sit-stand workstation, i.e. height-adjustable desk equipment allowing employees a choice of desk-based working positions will be provided to participants both the SS-O and SS-MC arms for 12-months. Participants will have the choice between two models of workstation (Ergotron Workfit-A or Workfit-D, www.ergotron.com). The lead researcher will explain the differences between the two workstations at the recruitment workshop, a flyer will be given to participants, and they will have the opportunity to ‘test out’ a demo workstation within their organisation before they choose their preferred workstation. Participants will receive written and verbal instruction on the correct ergonomic posture for both sitting and standing, upon installation of the workstations.

##### Individual level procedures

Participants in the SS-MC arm will receive four 5–10 minute telephone calls (before installation of the sit-stand workstation, and at weeks 3, 10 and 19) from the lead researcher who is experienced in motivational interviewing, as a method for “enhancing intrinsic motivation to change, by exploring and resolving ambivalence” [39]. These telephone calls will engage participants in conversations related to the sit-stand workstations and physical activity that will follow the principles of engaging, guiding and evoking to motivate and support participants to reduce their inactivity and increase activity, primarily at the workplace.

### Data collection

The research design is underpinned by the standard evaluation framework for physical activity programmes, incorporating both outcome and process evaluation data collection [40]. See Figure 1 for an overview of the data collection procedures.

#### Participant profile data

Profile data will be collected, through the expression of interest form (detailed earlier) and a short survey undertaken at a monitoring training session, before the installation of the sit-stand workstations. Questions on the short survey will include participants’ height, weight, job title, household composition, personal monthly income, level of education, and sexuality.

#### Outcome data

Primary outcomes are: daily time spent sitting, standing, in light and moderate-vigorous physical activity, the average number of sit-stand transitions per hour, number of prolonged sitting bouts ≥30 min, and total physical activity energy expenditure during work hours. Secondary outcomes will be the same, but over the course of the entire day (see Table 1)*.* These will be measured at baseline (approximately one month before sit-stand workstation installation) and four subsequent time-points following workstation installation; two-weeks, 3-months, 6-months and 12-months. Each data collection period will be 7-days. Sitting, standing and sit-stand transitions will be assessed using an ActivPAL3™ micro monitor (PAL Technologies Limited, Glasgow, UK) and light, moderate and vigorous physical activity will be assessed using an accelerometer (ActiGraph GT3X+, ActiGraph, Pensacola, FL, USA). The ActivPAL3™ provides accurate measures of sitting time and sit-to-stand transitions per hour and sit-stand transitions, when compared to direct observation in office-based free-living environments [41,42]. The ActivPAL3™ will be worn continuously on the centre of the right thigh, following insertion into a nitrile sleeve and wrapping in a waterproof dressing. Participants will be given extra materials to change the dressing when required. Participants will be requested to wear the monitor continuously for each 7-day data collection period. The ActiGraph GT3X+ is a tri-axial accelerometer that accurately classifies physical activity intensity in free-living environments [43]. It will be worn on the hip via an elastic belt during waking hours only, excluding time spent engaged in water-based activities. Participants will be asked to record non-wear time of both monitors, and time spent at the workplace for all 7-day data collection periods.

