## Abstract

**Background:**

A lack of physical activity and excessive sitting can contribute to poor physical health and wellbeing. The high percentage of the UK adult population in employment, and the prolonged sitting associated with desk-based office-work, make these workplaces an appropriate setting for interventions to reduce sedentary behaviour and increase physical activity. This pilot study aims to determine the effect of an office-based sit-stand workstation intervention, compared with usual desk use, on daily sitting, standing and physical activity, and to examine the factors that underlie sitting, standing and physical activity, within and outside, the workplace.

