One response to reducing sitting time in the workplace is the installation of sit-stand workstations. Sit-stand workstations offer height-adjustable desk equipment for computer screens and keyboards allowing employees a choice of desk-based working positions. Several studies have examined the contribution of sit-stand workstations to a range of sedentary behaviour, health and productivity outcomes. Previous sit-stand workstation intervention studies have seen varying reductions in the amount of time spent sitting, ranging from 66 minutes to 143 minutes per day [21]. A recent meta-analysis of activity-permissive workstations revealed that the reduction in sedentary behaviour is greater in interventions that incorporate a change to the working environment (i.e. an activity-permissive workstation), than interventions that do not [22]. Physiological research shows that using a sit-stand workstation for 185 minutes, immediately after eating, can reduce post-prandial glucose excursion by 43% [23]. A recent review of empirical studies examining the relationship between sit-stand workstations and a range of measures of productivity revealed that whilst the majority of studies show that using a sit-stand workstation had no influence on productivity, no studies showed a reduction in productivity [24]. In line with an ecological approach to behaviour change [25], initial research has shown that greater reductions in sitting time (56 min/8-hour workday) can be achieved as a result of a multi-component sit-stand workstation intervention (incorporating individual and organisational level components) compared to receiving a sit-stand workstation alone [26]. However, this needs to be replicated over a prolonged time-period (e.g. 12 months), on outcomes related to physical activity (distinct from sitting, standing and stepping). Whilst the feasibility of using sit-stand workstations has been qualitatively explored with desk-based office workers [27], outcome-focused studies dominate this research area. Understanding of the social processes that encourage and restrict standing and physical activity in the workplace is required. The absence of systematic and rigorous process evaluations of sit-stand workstation interventions will impede the wider adoption of sit-stand workstations across organisations [28,29].

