### Aims

The primary aim is to determine the effect of a 12 month multi-component sit-stand workstation intervention, incorporating organisational, environmental and individual level strategies, on physical activity within the workplace (primary outcome). Secondary aims are to: determine the effect of the sit-stand workstation intervention on physical activity outside of the workplace (secondary outcome), and to determine whether the multi-component intervention is more effective than the sit-stand workstation provision alone. The process evaluation will examine the factors that influence sitting, standing and active behaviours in the workplace.

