### Statistical methods

Two-way repeated measures ANCOVA will be conducted using IBM SPSS Statistics 20 to compare the outcome measures between study arms and across the intervention (between data collection time points). Relevant covariates will be controlled for, including body mass index.

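### The aim names one primary outcome (workplace physical activity) but the outcomes section names seven, with no lead variable or time point, one primary without a listed measure, and two different durations for the multi-component programme

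*Protocol article*

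**What the plan says.** - **Aims.** The primary aim is to "determine the effect of a 12 month multi-component sit-stand workstation intervention", and the effect is to be judged "on physical activity within the workplace (primary outcome". The comparison of the multi-component arm (SS-MC) with the workstation-only arm (SS-O) is placed among the secondary aims.
- **Background, last paragraph before Aims.** Earlier findings are said to need replication "on outcomes related to physical activity (distinct from sitting, standing and stepping".
- **Abstract, Background.** The aim is put more broadly: to "determine the effect of an office-based sit-stand workstation intervention, compared with usual desk use, on daily sitting, standing and physical activity".
- **Outcome data.** "Primary outcomes are: daily time spent sitting, standing, in light and moderate-vigorous physical activity, the average number of sit-stand transitions per hour", continuing with "number of prolonged sitting bouts ≥30 min, and total physical activity energy expenditure during work hours". Measurement is at baseline and at 2 weeks, 3, 6 and 12 months.
- **Table 1.** Nine variables are listed, four from the ActivPAL and five from the ActiGraph. Energy expenditure is not among them.
- **Theoretical basis and intervention development.** "The intervention will take effect for the first six-months following the installation of sit-stand workstations". The procedure sections agree with this: the last telephone call is at week 19 and the last managerial email at week 24. The workstation itself stays for 12 months in both intervention arms (Environmental level procedures).
- **Statistical methods.** A two-way repeated-measures ANCOVA is to be used "to compare the outcome measures between study arms and across the intervention (between data collection time points".

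**The concern.** A trial's primary outcome should be the same wherever the protocol states it. Here a reader who starts from the aim looks for one result on workplace physical activity. A reader who starts from the outcomes section looks for seven results, most of them on posture. These lead to different headline conclusions: a fall in sitting with no change in physical activity would count as a positive primary result under the outcomes section and as a null one under the aim.

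With no lead variable and no lead time point, the choice of headline can be made after the results are seen, in a trial whose researchers are not blinded to arm.

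The duration conflict has its own consequence. If the six-month schedule stands, a 12-month difference between SS-MC and SS-O measures whether an effect persists after the added components have ended. The wording of the aim would present the same number as the effect of a 12-month programme.

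**Working it through.** **1. Counting the primaries (Outcome data).** Sitting, standing, light activity, moderate-vigorous activity, sit-stand transitions per hour, prolonged sitting bouts, energy expenditure: 7.

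**2. Matching them to the aim.** Four (sitting, standing, transitions, prolonged bouts) describe posture. The Background separates physical activity from sitting, standing and stepping, so these four cannot simply be read as physical activity. That leaves 7 − 4 = 3 (light activity, moderate-vigorous activity, energy expenditure), each of which could represent the aim. None is chosen.

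**3. Checking that each primary has a measure.** Table 1 has 4 + 5 = 9 rows and none is energy expenditure. Outcome data assigns the ActivPAL to sitting, standing and transitions and the ActiGraph to light, moderate and vigorous activity. The ActivPAL3 and ActiGraph GT3X+ analysis sections describe posture bouts and count cut-points. None of these gives a measure or derivation for energy expenditure.

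**4. Time point.** There are four follow-ups. Neither Aims, Outcome data nor Statistical methods says which one decides the primary question.

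**5. Duration.** Aims says 12 months and the theoretical-basis section says the first six. The last scheduled contacts (weeks 19 and 24) fit the second statement. Only the workstation, common to SS-MC and SS-O, runs for 12 months.

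**6. Size of the multiplicity.** The protocol states no alpha, power or adjustment, so there is no figure of its own to reproduce. Assumptions: two-sided 5% per primary, no adjustment, one contrast at one time point.

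- Independent outcomes: 1 − (1 − 0.05)^7 = 1 − 0.95^7 = 0.302, about 30%.
- Equally correlated normal outcomes, by simulation under no effect (40,000 replicates):

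| Pairwise correlation | At least one false positive |
|---|---|
| 0.3 | 27% |
| 0.5 | 23% |
| 0.7 | 18% |
| 0.9 | 11% |

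The correlations are assumed, since the document gives none. Independence is the least plausible case because several of these variables come from one monitor over the same hours.

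**7. Cost of keeping all seven.** Bonferroni gives 0.05/7 = 0.0071 per test. With 30/3 = 10 per arm, the difference detectable with 80% power is (z for alpha + z for 80% power) × √(2/10). That is about 1.25 SD at 0.05 and about 1.58 SD at 0.0071 (normal approximation, no covariate gain, no dropout).

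**The case against.** The strongest defence is that this is a self-described pilot of 30 people with no formal power analysis, so strict familywise control matters less, and that adjustment and planned contrasts may sit in an analysis plan that is not shown. This lowers the severity. It does not remove the contradiction, because any analysis plan would still have to choose between the aim and the outcomes section. The aim is also worded as determining an effect, not as assessing feasibility.

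On duration, the defence is that the workstation is supplied for 12 months, that the schedule of added components is set out openly, and that the Discussion presents the long follow-up as a test of sustainability. That is fair, and a careful reader can work out what happens when. The wording of the aim still disagrees with the schedule.

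Four stronger readings are tempting, and the document does not support them.

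- **That there is no lead contrast.** Aims does rank the questions: the multi-component effect is primary and SS-MC versus SS-O secondary. Usual desk practice is the evident comparator from the abstract and Study design. The comparator is left to inference, but it is not absent.
- **That a chance positive is likely.** For seven tests the figures above stay at or below about 30%, well short of even odds.
- **That the plan entails 84 tests** (7 outcomes × 4 follow-ups × 3 arm pairs). Statistical methods describes a repeated-measures ANCOVA and does not commit to testing every such cell.
- **That the planned analysis is underpowered against a single contrast.** With assumed inputs (10 per arm, SD 80 min, within-person correlation 0.6, constant effects of −80 and −60 min), an arm-by-time test has about 59% power and one 12-month contrast about 76%. But the section does not make the interaction the deciding test. A baseline-adjusted arm effect over all follow-ups is also a repeated-measures ANCOVA and reaches about 93% on the same inputs.

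**Conclusion.** The concern holds as an inconsistency in the definition of the primary question. The primary outcome is stated in two incompatible ways, no lead variable or time point settles the matter, one stated primary has no listed measure, and the duration of the multi-component intervention is given as both 12 and six months. These four facts are read directly from the text and rest on no assumption.

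The error rate is secondary and conditional: about 30% for seven independent primaries, 18% to 27% at correlations from 0.7 down to 0.3, if each is tested once at an unadjusted 5%. Given the pilot status, this should be fixed and is not a fatal defect.

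**What to change.** Before any by-arm analysis:

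1. Name one primary variable that fits the aim, that is, one work-hours physical-activity measure listed in Table 1. If moderate-vigorous activity is chosen, say how it is formed, since the table lists moderate time, vigorous time and 10-minute bouts separately. If sitting time is what is really intended, amend the aim explicitly; making it primary without doing so would replace the stated aim.
2. State the primary contrast as SS-MC versus CG at one named time point.
3. Report the other outcomes and time points as secondary estimates with confidence intervals. SS-MC versus SS-O is already secondary and needs no move.
4. Remove energy expenditure from the primary list, or give its measure and derivation.
5. Reconcile the two statements of duration. If the six-month schedule stands, label a 12-month SS-MC versus SS-O difference as persistence after the added components end.

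The cost is a change to the protocol and registry wording, with a dated justification: Trial status says data collection has begun, and Randomisation says researchers are not blinded. The other variables lose primary status. Keeping all seven with Bonferroni would also limit the error rate, but would raise the detectable effect as shown in the working and still leave the aim unreconciled.

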**Table 1 Tab1:** **Study outcome measures taken at baseline, 2 weeks, 3 months, 6 months and 12 months**

	***Working hours***	***Total hours***
**ActivPAL3** **™**		
• Sitting time	✓	✓
• Number of prolonged (≥30 min) sitting bouts	✓	✓
• Number of sit-to-stand transitions	✓	✓
• Standing time	✓	✓

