**ActiGraph (GT3X+)**		
• Time in light physical activity (min)	✓	✓
• Time in moderate physical activity (min)	✓	✓
• Time in vigorous physical activity (min)	✓	✓
• Time in MVPA in 10-min bouts (min)	✓	✓
• Counts per minute	✓	✓

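### The only prolonged-sitting outcome, a count of bouts of 30 min or more, can rise or fall when long sitting is broken up; transitions have two definitions, and time outcomes no stated denominator

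*Protocol article*

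**What the plan says.** Under Outcome data, the protocol article names among its primary outcomes, for work hours, "the average number of sit-stand transitions per hour, number of prolonged sitting bouts ≥30 min". The secondary outcomes are the same measures over the whole day. Table 1 repeats the bout measure as "Number of prolonged (≥30 min) sitting bouts" for both periods. Neither place lists the minutes accumulated in such bouts.

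Transitions are a rate per hour in the Outcome data text, but Table 1 gives "Number of sit-to-stand transitions" with no time unit.

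The time outcomes are "daily time spent sitting, standing, in light and moderate-vigorous physical activity" in the text and minutes in Table 1, for example "Time in light physical activity (min". No denominator is stated. One ActiGraph outcome in Table 1, "Counts per minute", is already scaled to time. Participants log non-wear of both monitors and their hours at the workplace (Outcome data), but no use of these logs as a denominator is described. The Background quotes an earlier result in standardised form: "greater reductions in sitting time (56 min/8-hour workday".

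**The concern.** The Background gives lack of breaks in sedentary time as a risk in its own right, and the Discussion sets reduction of prolonged sitting as a goal. A measure of prolonged sitting should therefore move one way when long sitting is interrupted. A count of bouts above a threshold does not. Splitting one very long bout into pieces that each still pass 30 min adds to the count; splitting it more finely removes pieces from it. The same improvement in behaviour can show as a worse or a better primary outcome, depending on how long the bouts were at the start.

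The other two matters are smaller. A rate and a plain number of transitions differ whenever hours differ, so one primary outcome has two definitions. Minutes without a denominator vary with the length of the working day, and for the hip monitor with wear, as well as with behaviour.

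**Working it through.** **Inputs.** From the protocol article: the 30 min threshold (Outcome data, Table 1); 81.8% of work hours sedentary (Background); N = 30 in three equal arms, so 30/3 = 10 per arm (Sample size, Randomisation). Assumed: break lengths, break rates, the 480 min of sitting, hours worked or worn, and the shares of time other than 81.8%. The plan has no target difference and no power calculation, so there is no figure of its own to reproduce.

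**1. The basic example.** Four hours unbroken: 1 bout, 240 min. Four hours with 5 min standing in each: 4 bouts of 55 min, 4 × 55 = 220 min. The count goes from 1 to 4 while sitting falls by 240 − 220 = 20 min.

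**2. Equal pieces.** Take a block of L min with k stands of 2 min (assumed). Piece length = (L − 2k)/(k + 1). The count is k + 1 if the piece is at least 30 min, otherwise 0.

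| L (min) | Breaks k | Piece (min) | Count | Minutes in bouts ≥30 |
|---|---|---|---|---|
| 60 | 0 | 60.0 | 1 | 60 |
| 60 | 1 | 29.0 | 0 | 0 |
| 120 | 0 | 120.0 | 1 | 120 |
| 120 | 2 | 38.7 | 3 | 116 |
| 120 | 3 | 28.5 | 0 | 0 |
| 240 | 0 | 240.0 | 1 | 240 |
| 240 | 6 | 32.6 | 7 | 228 |
| 240 | 7 | 28.2 | 0 | 0 |

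The count goes up, then collapses. The minutes only go down, and this holds in general: the pieces of a split bout that still reach 30 min cannot add up to more than the bout they came from.

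**3. Random breaks.** Take 480 min of sitting with breaks of negligible length at random (Poisson), 20,000 simulated days per rate.

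| Breaks per hour | Mean count | Mean minutes in bouts ≥30 |
|---|---|---|
| 0 | 1.0 | 480 |
| 0.5 | 3.7 | 462 |
| 1 | 5.2 | 428 |
| 2 | 5.9 | 342 |
| 4 | 4.2 | 187 |
| 6 | 2.3 | 91 |

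With λ breaks per minute the expected count is exp(−30λ) × [1 + λ(480 − 30)]. At 2 per hour, λ = 1/30, this is exp(−1) × 16 = 5.9, as simulated. The count peaks near 2 breaks per hour. To the left of that, more breaks raise it; to the right, they lower it.

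**4. Denominators.** Sitting for 81.8% of 8 h is 0.818 × 480 = 392.6 min. Sitting for 75% of 9 h is 0.75 × 540 = 405.0 min, so the share falls while the minutes rise. At 70% of 9 h, 0.70 × 540 = 378.0 min, both fall. A reversed sign therefore needs a shift in hours that is large relative to the effect.

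For chance imbalance, assume that mean daily work time has a between-person SD of 30 to 60 min. The standard error of the difference between two arms of 10 at one visit is SD × √(2/10), which is 13 to 27 min of work time. Multiplied by 0.818 this is 11 to 22 min of raw sitting.

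**The case against.** **The count does not always go the wrong way.** This stands. A reader might infer that breaking up long sitting raises the count as a rule. It does not: one break in a 60 min bout takes it from 1 to 0. Which side of the peak these participants start from depends on a baseline break rate that the article does not give. The defect is ambiguity of direction, not a consistent bias.

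**Other outcomes would show the pattern.** Total sitting time and transitions per hour are also primary, and read together they would help to explain a rising count. This is fair, but neither measures prolonged sitting, and a reader of the count alone could draw the wrong conclusion.

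**Scaling may sit in an analysis plan that is not shown.** This largely stands. The article is silent on standardisation and does not rule it out. It collects the logs that scaling needs, leaves the ActiGraph non-wear rule to be developed, and allows for covariates beyond body mass index. Nor are all outcomes unscaled: counts per minute and, in the text, transitions per hour are rates.

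**Unequal hours as a bias.** A reader might reason that 30 min more at work adds 0.818 × 30 = 24.5 min of sitting, which is 24.5/56 = 44% of the effect quoted in the Background, and call this the bias. The documents do not support that. It needs arm means that differ by 30 min, whereas participants are full-time staff randomised within organisation, and nothing suggests that hours respond to the intervention. The 56 min is also the extra reduction from the multi-component programme over the workstation alone. Against the 66 to 143 min per day quoted for workstation studies, 24.5 min is 37% to 17%. Unequal hours are mainly added noise or chance imbalance.

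**Conclusion.** The point holds for the bout count. It is the sole measure of prolonged sitting, it is a primary outcome, and it is non-monotone. In the worked example it rises fourfold while sitting falls by 20 min; under random breaks it rises from 1.0 to 5.9 and then falls to 2.3, while minutes in bouts of at least 30 min decline at every step. The sizes rest on assumed break patterns. The non-monotonicity does not; it follows from the definition.

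The mismatch between transitions per hour and number of transitions is a plain inconsistency to be reconciled. The missing denominator is the weakest part. With about 10 people per arm, stating one would remove avoidable noise, but its absence from the article is not evidence that the analysis will ignore hours. None of this invalidates the trial; it limits what a change in the count can be taken to mean.

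**What to change.** 1. Add minutes accrued in sitting bouts of at least 30 min, in work hours and over the whole day, as the main measure of prolonged sitting. Keep the count as a reported companion; dropping a stated primary outcome once data collection has begun (Trial status) would be harder to defend than adding a measure.
2. Define transitions per hour in both the Outcome data text and Table 1.
3. Report work-hours sitting, standing and activity minutes per 8 hours of logged work time, and for the ActiGraph per 8 hours of logged and worn work time. Give raw minutes as descriptive results.

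Cost: one more derived outcome and a dated, documented amendment, best made before any comparison between arms. No new data are needed, because the ActivPAL3 stores the length of each bout (Data analysis) and workplace and non-wear times are already logged.
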